### 2) Among People who Wanted Sterilization at Time 2 but Did Not have Sterilization at T3:

- What are their Reasons for Contraceptive Method(s) Mismatch: a series of logistic regressions will be used to test intervention effects on *reasons for mismatch* controlling for study site and potential confounders
  - We specifically hypothesize that intervention group members will be less likely to report logistical barriers.
    - Logistical barriers are defined as any of the following reasons: Financial concerns, Method was unavailable/too difficult to obtain, Method was too difficult to use

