| Method was unavailable/too difficult to obtain                                                            | For people who reported at T2 wanting a method other than sterilization but their current contraception doesn't match                                                                                                                            | T3 | Dichotomous (yes/no) | Dichotomous (yes/no)                             |
| You were concerned about the side effects                                                                 | For people who reported at T2 wanting a method other than sterilization but their current contraception doesn't match                                                                                                                            | T3 | Dichotomous (yes/no) | Dichotomous (yes/no)                             |
| Method was too difficult to use                                                                           | For people who reported at T2 wanting a method other than sterilization but their current contraception doesn't match                                                                                                                            | T3 | Dichotomous (yes/no) | Dichotomous (yes/no)                             |
| You were concerned about its effectiveness/it would not prevent pregnancy                                 | For people who reported at T2 wanting a method other than sterilization but their current contraception doesn't match                                                                                                                            | T3 | Dichotomous (yes/no) | Dichotomous (yes/no)                             |
| Your partner did not like this method                                                                     | For people who reported at T2 wanting a method other than sterilization but their current contraception doesn't match                                                                                                                            | T3 | Dichotomous (yes/no) | Dichotomous (yes/no)                             |

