| The consent form was not completed on time or in its entirety                                             | For people who reported at T2 wanting sterilization as their method but did not undergo sterilization                                                                                                                                            | T3 | Dichotomous (yes/no) | Dichotomous (yes/no)                             |
| The operating room was not available                                                                      | For people who reported at T2 wanting sterilization as their method but did not undergo sterilization                                                                                                                                            | T3 | Dichotomous (yes/no) | Dichotomous (yes/no)                             |
| The wait between your delivery and getting the procedure was too long                                     | For people who reported at T2 wanting sterilization as their method but did not undergo sterilization                                                                                                                                            | T3 | Dichotomous (yes/no) | Dichotomous (yes/no)                             |
| You decided you wanted a reversible method of contraception                                               | For people who reported at T2 wanting sterilization as their method but did not                                                                                                                                                                  | T3 | Dichotomous (yes/no) | Dichotomous (yes/no)                             |

|                                               |                                                                                                              |    |                      |                                                  |
|-----------------------------------------------|--------------------------------------------------------------------------------------------------------------|----|----------------------|--------------------------------------------------|
|                                               | undergo sterilization                                                                                        |    |                      |                                                  |

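### The logistical-barriers composite for women who wanted sterilization but did not have it takes two of its three items from another group's list, so it reduces to financial concerns

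*Combined protocol and SAP*

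**What the plan says.** The section Exploratory Analyses in Specific Subset(s) of the Sample, item 2, sets the population in its heading: "Among People who Wanted Sterilization at Time 2 but Did Not have Sterilization at T3". It plans a series of logistic regressions on the reasons for mismatch, adjusted for site and potential confounders, and adds one directional hypothesis: "We specifically hypothesize that intervention group members will be less likely to report logistical barriers". The composite is then fixed: "Logistical barriers are defined as any of the following reasons: Financial concerns, Method was unavailable/too difficult to obtain, Method was too difficult to use".

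The Exploratory Outcome Measures table holds two separate lists of T3 reasons, and each row names the women it applies to. The items "Method was unavailable/too difficult to obtain" and "Method was too difficult to use" both carry this label: "For people who reported at T2 wanting a method other than sterilization but their current contraception doesn't match". The list for women who wanted sterilization at T2 and did not undergo it includes "The consent form was not completed on time or in its entirety", "The wait between your delivery and getting the procedure was too long" and an item on operating room availability. Financial concerns appears on both lists.

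**The concern.** The composite is defined for one group with items that the outcome table assigns mostly to the other. Followed literally, the analysis would report an effect on logistical barriers that is in fact an effect on financial concerns alone. The reasons most naturally called logistical for a postpartum procedure would fall on the no-barrier side of the outcome.

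The Research Background makes the mismatch harder to dismiss. It describes the mandatory waiting period and the need to get the consent form to the delivery suite as logistical obstacles to a desired procedure. An item on the consent form is listed for exactly this subset, yet the composite leaves it out. At stake are the meaning and the label of the only directional hypothesis in this subset.

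**Working it through.** The plan states no figure for this analysis, so there is none to reproduce. The check compares the composite with the two reason lists in Exploratory Outcome Measures.

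**Step 1. The lists.** Each has nine reasons.

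- Wanted a method other than sterilization at T2: medical; financial; unavailable or hard to obtain; side effects; hard to use; effectiveness; partner's dislike; no STI protection; something else.
- Wanted sterilization at T2 but did not undergo it: medical; financial; consent form incomplete or late; operating room unavailable; wait after delivery too long; decided on a reversible method; anesthesia; recovery; other (open-ended).

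Only the medical and financial items are on both lists.

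**Step 2. The composite against each list.**

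| Composite item | Listed for the other-method group | Listed for the sterilization group |
|---|---|---|
| Financial concerns | yes | yes |
| Unavailable or too difficult to obtain | yes | no |
| Too difficult to use | yes | no |
| Total | 3 of 3 | 1 of 3 |

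**Step 3. What an any-of rule gives in the stated subset.** Let F be Financial concerns, and let U and D be the two items not listed for these women.

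- If U and D are set to 0, then composite = max(F, 0, 0) = F. The result is financial concerns under a wider name.
- If U and D are left missing, F = 1 gives 1, but F = 0 gives an undefined value. Women without financial concerns drop out, leaving no zeros to compare with.

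The plan does not say which coding applies.

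**Step 4. Who is misclassified.** Under the first coding, a woman whose only reason is the consent form, the operating room or the wait has F = 0 and is counted as having no logistical barrier. The documents give no expected size for the subset and no frequency for any reason, so the number of such women cannot be estimated.

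**Step 5. Support for the omitted items.** The Research Background's logistical obstacles correspond directly to the consent-form item. Its waiting period is the 30 days required before surgery. The wait in the T3 item runs from delivery to the procedure, so the match there is looser. The operating-room and wait items are logistical on their face, but the documents do not label them so.

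**The case against.** The strongest reply is that little depends on this. The subset is defined by two events after randomization (T2 preference and T3 non-receipt), and the plan itself says that analyses in such subsets no longer rely on randomization and need confounder control. The same item plans a series of regressions on reasons for mismatch, so the consent-form, operating-room and wait reasons can be analysed one at a time. The open-ended mismatch question, the other-reason item and the question on why a signed consent was not followed by sterilization are content-analysed as well. All of this stands, and it limits the severity. It does not rescue the composite: the stated hypothesis rests on it, and choosing after the data are seen which reasons count as logistical would lose the value of having specified it.

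A second reply is that the heading may be what is misplaced, since all three composite items are on the other group's list. That is possible, and no corresponding regression is planned for that group. The conflict between the two sections remains either way.

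A reader might also infer more than the documents support:

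- *That the hypothesis cannot be tested at all.* Financial concerns is listed for this subset, so the regression can be run if the unlisted items are counted as absent. It tests something narrower than its label.
- *That these women are never asked the two items.* The T3 questionnaire and its skip pattern are not in the documents. The table shows only that the items are not listed for this group.
- *That the result would be wrong in a known direction.* No direction or size of bias can be derived.
- *That logistical barriers are the reason for the trial.* The Research Background raises both informed decision making and access. The objectives concern knowledge, decisional conflict, method selection and satisfaction.

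**Conclusion.** Wrong as written, of moderate severity, and confined to one exploratory analysis. Two of the three composite items are not listed for the women in whom the composite is to be analysed. It reduces to Financial concerns, or is undefined for women without financial concerns, while being reported as logistical barriers. Three reasons listed for this subset (consent form, operating room, wait) are left out, so the hypothesis is not tested as intended. Primary and secondary outcomes and the sample size are unaffected.

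Two assumptions underlie this. The questionnaire is taken to follow the population labels in the outcome table. Calling the three omitted reasons logistical is a judgement, which the Research Background supports directly for the consent form; for the other two it rests on their plain meaning.

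**What to change.** Before any analysis by arm, reconcile item 2 of the subset analyses with the two lists in Exploratory Outcome Measures. For women who wanted sterilization at T2 but did not have it by T3, define a logistical barrier as a yes to at least one of four items on their own list:

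- Financial concerns
- "The consent form was not completed on time or in its entirety"
- the item on the operating room not being available
- "The wait between your delivery and getting the procedure was too long"

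Keep the present three-item definition only for women who wanted a non-sterilization method at T2, if a composite is wanted there. If that group was the one intended, correct the heading of item 2 instead.

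The cost is about one line of SAP text. Every item is already listed for collection at T3, so neither data collection nor sample size changes.

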### 3) Among people who had sterilization counseling:

- What is Participant Satisfaction with Sterilization Counseling at Time 3: linear regression to test intervention effects controlling for study site and potential confounders
  - Compared to women who receive usual care alone, women randomized to the decision aid arm will report greater satisfaction with sterilization counseling at Time 3

[figure not shown]

